## Abstract

**Background:**

The incidence and prevalence of type 2 diabetes (T2DM) are expected to continue rising. T2DM causes life-threatening, disabling and costly complications, and significantly reduces quality of life and life expectancy. The burden of T2DM can be reduced using comprehensive lifestyle modifications. The aim of this study is to evaluate the applicability and cost-effectiveness of a multicomponent, multidisciplinary lifestyle program in 22 European regions and to generate guidelines for transfer to European health care systems.

**Methods:**

A quasi-experimental study (without a control group) will be conducted to evaluate the CARE4DIABETES program, which is based on the Reverse Diabetes 2Now best practice. The program will involve more than 120 healthcare professionals and 860 people with T2DM from 12 European countries - Belgium, Bulgaria, Finland, Hungary, Italy, Greece, Malta, Poland, Portugal, Slovakia, Slovenia and Spain. Patients will be enrolled based on clinical criteria and motivation for change. The program will have two phases, an intensive phase (6 months) with face-to-face and online training to achieve behavioral change, and an online aftercare phase (6 months) to consolidate changes. The program will be evaluated for impact, sustainability and cost-effectiveness using a combination of validated questionnaires at baseline, six months and one year after the start of the intervention.

**Clinical trial number:**

Trial registration number: ISRCTN62063346.

## Introduction

Type 2 diabetes mellitus (T2DM) is a highly heterogeneous non-communicable chronic disease with a variable age of onset, associated with an undetermined degree of obesity and insulin resistance, and with tendency to develop health- and life-threatening complications [1]. Widespread worldwide, T2DM is already one of the major public health challenges for middle- and high-income countries [2]. Although the underlying causes of T2DM are a puzzle with genetic, physiological, and behavioural pieces -some of which remain unknown-, probably lifestyle-related factors are the dominant cause. Therefore, a comprehensive approach for people living with T2DM should pursue long-lasting lifestyle modifications [3].

There is robust evidence on the efficacy of a wide range of interventions to improve glycaemic control and self-management disease via changes in relevant health-related behaviours, including adherence to pharmacological treatment and to healthy lifestyle, which theoretically lead to long term improvements in T2DM progression [4]. Some examples of effective interventions include among the others: programs to enhance health literacy, disease information and skills of e-health strategies, such as gamification, use of wearable devices or telemonitoring; peer-led interventions; mind practices to reduce stress [5–14].

There is also a growing body of evidence for T2DM remission, that can be achieved through intensive behavioural interventions, alone or combined with bariatric surgery or pharmacological interventions [15–17]. T2DM remission is considered when maintaining glycated haemoglobin below 6.5% without pharmacological treatment for three months [18], and it has been recognized by the World Health Organization and scientific associations as an appropriate therapeutic goal [19]. However, according to the American College of Lifestyle Medicine, therapeutically dosed intensive lifestyle modifications should be preferentially recommended as the primary modality for T2DM care and remission [20]. Interventions should include personalized nutrition coupled with physical activity engagement as ways to reach weight loss [19]. However, long-term weight regain is the usual hurdle encountered by patients and clinicians in the real-world setting, as the difficulty of long-lasting restricted diets, such as very low-calorie or nutritional ketosis diets, hinders the sustainability of any potential results. Therefore, studies targeting different populations on the efficacy of various complementary strategies for weight management, including mental stress and sleep disorders [21], are required [19]. Additionally, the American Diabetes Association has introduced another recommendation for the inclusion of technology assisted T2DM programmes based on patients’ preferences [22].

Against this background, a multicomponent and multidisciplinary programme called “Reverse Diabetes 2Now” (RD2N) was developed in The Netherlands seeking remedy for T2DM [23]. RD2N focuses on improving participant skills -rather than just knowledge- to manage relevant components of their lifestyle, regaining control over their disease. In essence, RD2N is a 6-month programme that provides intensive group-based counselling on nutrition, physical activity, sleep and stress management, biometric feedback, and cooking classes, combined with a digital coaching platform and close physician-monitoring of medication use. In preliminary studies, RD2N has demonstrated lasting real-life benefits, especially in terms of body weight, medication use and quality of life in people living with T2DM [24].

RD2N was selected by the European Union as best practice in primary care, to be tested as a joint action in different countries. CARE4DIABETES - Reducing the burden of non-communicable diseases by providing a multi-disciplinary lifestyle treatment intervention for T2DM - was the name given to the joint action. Therefore, CARE4DIABETES (C4D) was conceived as a comprehensive and structured framework to design, adapt, implement and evaluate the RD2N best practice in the EU, seeking for a sustainable reduction in the burden of T2DM and its related risk factors, both at societal and personal level, as well as raise awareness and acceptance on improved and more innovative related lifestyle interventions, in line with EU policy framework and the Action Plan for Prevention and Control of Non Communicable Diseases in the World Health Organization (WHO) EU Region 2016–2025 [25].

This paper describes the study protocol of C4D to transfer the RD2N best practice into 12 selected European countries: Belgium, Bulgaria, Finland, Hungary, Italy, Greece, Malta, Poland, Portugal, Slovakia, Slovenia, and Spain. Conclusions about acceptance and effectiveness in different contexts will allow the production of guidelines for transferability of the intervention in the EU.

## Methods

### Design and ethical considerations

C4D will be a one-group pre-test/post-test quasi-experimental study, conducted in concert in 12 countries. Briefly, C4D will evaluate the acceptability and efficacy of an innovative multicomponent intervention addressing several lifestyle behaviours (i.e. nutrition, physical activity, sleep, and stress management), that can trigger the achievement of long lasting body weight control, healthy glucose levels, lowering -and in some cases interrupting- medication consumption, reducing comorbidities, complications and associated healthcare costs, and improving health-related quality of life. The intervention will be based on the “Integrated Model for explaining motivational and behavioural change” (I-CHANGE model) and will focus on improving participants’ skills - not just knowledge - to manage relevant components of their lifestyle [26]. The structured implementation process, including training and capacity building of healthcare personnel and cultural adaptation according to local situation, aims to produce a sustainable lifestyle care model that can be scaled up nationally. Each country/partner will have a local multidisciplinary team in charge of driving the process, consisting of at least a diet expert, registered nurse or general practitioner, a coach, facilitator or equivalent and a lead coordinator (Table 1). The C4D will run from February 2023 to January 2026.

**Table 1 Tab1:** Roles and functions of the intervention team by voeding Leeft foundation

Role	Responsibilities in RD2N practice	
Diet expert	• Physiological explanation of the metabolic disturbance of type 2 diabetes (insulin resistance). • Guidance for participants in changing eating habits.	
Registered Nurse or General Practitioner	• Safe process guidance for individual participants. • Individual and group guidance on reduction of medication and reversing type 2 diabetes. • Manage participant record and registration. • Contact with the lead practitioner of the participant.	
Coach/facilitator or equivalent	• Create a safe setting for the individual and the group. • Activate and monitor group dynamics. • Guidance in awareness and behavioural change. • Guide to activation and integration of sustainable behaviour.	
Coordinator	• Quality assurance. • Practical organization of the program • Communication with participants. • Administration participants and keeping overview of progress.	

The study has been approved by an ethics committee (EC) in each participating country to conduct the activities in accordance with EU ethical standards. Study participants must sign the informed consent form before starting the proposed activities. Previously, they will have received, through an information sheet and interview with the assigned professional of reference, all the related information, as to resolve any doubt that may arise beforehand. Since behavioural changes are expected from the beginning of the program, the first pharmacological reduction of antidiabetic agents should be carried out early during the first intervention sessions unless EC and/or clinicians recommended differently for a specific country. Further medication modifications will be made during the program based on the biometric levels of the participants. Thereby, C4D will be implemented under strict (and continuous) medical supervision.

### Stages/Sequencing actions

The study protocol is divided in different stages and each of them applies different approaches to ensure its scientific soundness (Fig. 1).

**Fig. 1 Fig1:**
[figure not shown]
Sequence of stages of C4D

#### Preparatory actions

The challenge of transferring a particular contextualized successful practice into a different environment along the EU requires a deep knowledge of the original RD2N best practice. But at the same time, the uniqueness of each context needs to be analysed to provide the best opportunity to transform RD2N best practice into a local real possibility. Therefore, preparatory actions include a comprehensive analysis of general aspects to be considered by the local teams when adapting, implementing, monitoring, and evaluating the RD2N best practice. They also involve the examination of country-specific circumstances, including key stakeholders’ identification as local facilitators of the entire process. Different methodologies will be applied: (a) SCIROCCO [27], self-assessment tool which will be used to identify the maturity of the health and social care systems, for the adoption and scaling up of integrated care, or best practice solutions; (b) Consolidated Framework for Implementation Research (CFIR), a construct to analyse determinants [28]; it is designed to describe barriers and facilitators to implementation outcomes; (c) SQUIRE 2.0, a framework for reporting new knowledge about the actions and how to improve healthcare [29]; (d) SWOT analysis (acronym of strengths, weaknesses, opportunities and threats), a technique for assessing the national, regional and local contexts, including stakeholders [30], which can help to analyse what each partner does best now, and to devise a successful strategy for the future.

During this preliminary stage, up to 120 healthcare professionals (i.e. up to 10 *per* country) are directly trained by Dutch RD2N best practice owner for their actions in their countries. The training is designed online over 5 sessions with all selected members of the multidisciplinary team per each country (together), that will receive the “know how” to transmit to people with T2DM the fundamental elements of the intervention. Three formations have been planned with four countries in each formation to effectively deliver the training. Then, local multidisciplinary team members will adapt the content and materials to their respective local languages and context. The main materials that need adaptation are: the participant’s book, recipe book, formative content of the intervention sessions and entries on the digital platform.

#### Recruitment of participants

People with a physician-diagnosed T2DM will be invited by the healthcare worker in charge of their follow-up, who will previously determine the compliance with selection criteria. A candidate will be considered for participation if he/she meets all eligibility criteria (Table 2). People already selected must be informed in detail about their participation and commitments and signed the consent form; they must fill in baseline registration forms to be compared with new forms required as their participation progresses.

**Table 2 Tab2:** Eligibility criteria for participants

Age 20–80 years
T2DM treated with medication (oral or injected medicines or insulin)
T2DM duration 1–10 years
BMI 25–40 kg/m^2^
No COPD or kidney or heart failure diagnosis
No bariatric surgery (self-reported/medical record)
No eating disorder (self-reported /medical record)
No pregnancy (self-reported /medical record)
Committed to make lifestyle changes to control T2DM
Ability to use necessary digital devices
Access to internet
Sufficient language skills to take part in the program
Possibility to take part in the program as provided (schedule, location)
Willingness to measure blood glucose at home

T2DM: type 2 diabetes mellitus, BMI: body mass index; COPD: chronic obstructive pulmonary disease

According to C4D study protocol, 860 people living with T2DM are expected to be recruited, with a minimum of 40 participants *per* country (Fig. 2). An estimation was done considering body weight as main outcome. Based on the 6-month body weight reduction results from the original best practice, with standard deviation of 5.1 kg, we can estimate that a sample size of 40 participants is sufficient for a paired sample t-test (power of 80%, type 1 error rate 0.05), assuming the true effect size (mean reduction in body weight during the first 6 months) is 2.3 kg. Therefore, 860 participants will be enough to test the hypothesis involving health-related quality of life.

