The process evaluation considers the satisfaction and experience of participants and staff, using a self-reported questionnaire. The evaluating process follow the RE-AIM framework (Table 4). In addition to the quantitative parameters, qualitative data collect factors influencing participation/non-participation; elements contributing the outcomes; the barriers preventing adoption (both by care providers and participants); how was the intervention implemented; and what will be sustained, discontinued, or adapted, and why.

**Table 4 Tab4:** Components of RE-AIM framework

Component	Indicator
Reach	
*Inclusion*	Activities/procedures to attract possible participants
	Number of potential participants screened for eligibility
*Exclusion*	Number of potential participants excluded (per exclusion criterion)
*Background characteristics*	Characteristics of participants compared to non-participants or to target population
Effectiveness	
	Number of sessions/hours of intervention organized
	Number of intervention sessions/hours of intervention attended by each participant
	Attrition (%)
	Outcome measures (%) completed at each timepoint
Adoption	
	Characteristics of settings participating compared to non- participants
	Number (and %) of staff participating
	Characteristics of staff participants vs. typical staff
Implementation	
	Adaptations made to intervention (Phase 1)
	Cost of intervention
	Consistency of implementation across staff/settings
Maintenance	
	Outcome measures at 12 months
	Adaptations made to intervention (Phase 2)
	Model integration to the organization

Socio-demographic characteristics such as sex, age, education, immigrant background, cohabitation and income level will be analysed.

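### The country minimum of 40 serves both as the number recruited and as the number of pairs behind 80% power, with no allowance for attrition

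*Protocol article*

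**What the plan says.** The sample-size paragraph of the protocol article (Methods, Recruitment of participants) uses the number 40 twice. It first sets the recruitment target: "860 people living with T2DM are expected to be recruited, with a minimum of 40 participants" in each country. It then gives the justification, which takes body weight as the main outcome: "a sample size of 40 participants is sufficient for a paired sample t-test (power of 80%, type 1 error rate 0.05". The inputs are a standard deviation taken from the original Dutch programme ("Based on the 6-month body weight reduction results from the original best practice, with standard deviation of 5.1 kg") and an assumed effect ("assuming the true effect size (mean reduction in body weight during the first 6 months) is 2.3 kg"). The article does not say whether the test is one- or two-sided.

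Neither that paragraph nor any other part of the article gives an expected dropout rate or inflates the number for loss. Table 4 (Evaluation) does list attrition among the indicators to be recorded, together with "Outcome measures (%) completed at each timepoint".

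**The concern.** The two uses of 40 count different people. The first counts those who enter the study. The second has to count those with a weight at baseline (T1) and again at 6 months (T2), because a paired t-test has nothing to work with when one of the two is missing. The two counts agree only if nobody is lost over 6 months. That is hard to assume for a programme of repeated group sessions, including an overnight stay in the face-to-face mode, and the plan itself intends to measure attrition.

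Power within a country matters because the article wants conclusions on acceptance and effectiveness in different contexts, as a basis for transfer guidelines. If a country at the minimum has less power than stated, a real 2.3 kg reduction there is more likely to be missed, and a non-significant result could be misread as a failure to transfer.

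**Working it through.** **Inputs from the article (Recruitment of participants).** Mean reduction 2.3 kg; standard deviation 5.1 kg, read as that of the paired change; type 1 error 0.05; power 80%; n = 40; total 860 in 12 countries.

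**Assumptions.** Two-sided testing, since sidedness is not stated and the two-sided calculation reproduces the article's figure. Loss of T2 weights of 10%, 20% or 30%, since the article gives no rate.

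**Step 1. Reproduce the stated figure.**
- Standardised effect: 2.3 / 5.1 = 0.451.
- Normal approximation: n = (5.1 × (1.960 + 0.842) / 2.3)² = 38.6, so 39.
- Exact calculation (noncentral t, n − 1 degrees of freedom, noncentrality 0.451 × √n): 40 pairs give 79.4% and 41 pairs give 80.4%.

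The article's 40 and 80% are therefore reproduced within rounding. They are reproduced for 40 complete pairs, with nothing to spare.

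**Step 2. Start from 40 recruited and lose some T2 weights.**

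| Recruited | Loss by T2 | Complete pairs | Two-sided power for 2.3 kg | Effect detectable with 80% power |
|---|---|---|---|---|
| 40 | 0 | 40 | 79.4% | 2.32 kg |
| 40 | 1 person | 39 | 78.4% | 2.35 kg |
| 40 | 5% | 38 | 77.3% | 2.38 kg |
| 40 | 10% | 36 | 74.9% | 2.45 kg |
| 40 | 20% | 32 | 69.6% | 2.61 kg |
| 40 | 30% | 28 | 63.3% | 2.80 kg |

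**Step 3. Recruitment needed to keep 40 pairs.** The formula is 40 / (1 − loss), rounded up:
- 10% loss: 40 / 0.9 = 44.4, so 45.
- 20% loss: 40 / 0.8 = 50.
- 30% loss: 40 / 0.7 = 57.1, so 58.

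**Step 4. How far the problem reaches.**
- If every country recruited only the minimum, the total would be 12 × 40 = 480. The target of 860 implies a mean of 860 / 12 = 71.7 per country.
- An average country losing 40% keeps 71.7 × 0.6 = 43 pairs, which still gives 82.4%.
- The pooled sample losing 40% keeps 860 × 0.6 = 516 pairs, and power for 2.3 kg is near 100%.

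The shortfall is therefore confined to country-level tests in countries that recruit at or near 40. The country minimums are in Fig. 2, which is not available here, so the number of such countries cannot be given.

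**The case against.** **No figure is miscalculated.** That is right. The stated power reproduces, and losing one pair leaves 78.4%. It would be wrong to say that any dropout falsifies the 80%. The gap becomes material at moderate loss: more than 2 points from two lost pairs, about 5 points at 10% and about 10 points at 20%.

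**Most countries should recruit more than 40, and the pooled analysis is safe.** Both parts stand, and they limit the point to countries near the minimum. They do not remove it, because the 40 is offered as a sufficient number for a country.

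**Sidedness is open.** With one-sided testing, 32 pairs would give 80.2%, so a 20% loss would be absorbed. But one-sided testing at 40 pairs would give 87.6%, which is not the stated figure. The two-sided calculation is the one that fits.

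**Table 4 gives no expected rate.** Correct. Its entries are process indicators, so the 10% to 30% range is an assumption of this review.

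**Missing-data handling may sit in a document not shown.** This also stands. A reader might go further and infer that the planned analysis drops people without a T2 weight and so overstates the weight loss. The article does not support that inference. It names the paired t-test only to size the study, and it gives no data on weight change in people who leave. If completers lose 2.3 kg and 20% are lost, the mean over everyone is 0.8 × 2.3 + 0.2 × m, where m is the mean loss in dropouts. That is 1.84 kg for m = 0, 2.30 kg for m = 2.3 and 2.44 kg for m = 3.0. The bias could be upward, nil or downward, so no finding is made on it and no analysis method is asked for.

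**Conclusion.** The point holds as one about the stated sample-size justification. The recruitment minimum equals the number of complete pairs that the power calculation needs, and nothing is allowed for attrition. A country recruiting exactly 40 would have about 75%, 70% or 63% power at 10%, 20% or 30% loss, instead of the stated 80%. At 20% loss, the chance of missing a true 2.3 kg reduction is about 30% rather than 20%.

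This rests on two-sided testing at 0.05, on 5.1 kg being the standard deviation of the paired change, and on loss rates that the article does not give. It does not extend to the pooled analysis or to countries well above the minimum. It is worth correcting because the article presents 40 as enough for a country, and country-level findings feed the transfer guidelines.

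**What to change.** State in the sample-size paragraph which 40 is meant, and that the test is two-sided if that is the intention. Any one of these would do:

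- Say that 40 is the number of participants per country with both a T1 and a T2 weight.
- Keep 40 as the recruitment minimum and restate the power. For example: *40 per country is the recruitment minimum; 40 complete T1–T2 pairs give about 79% power for 2.3 kg, and with 20% loss about 70% power for 2.3 kg, or 80% power for about 2.6 kg (two-sided).* The 20% should be replaced by the sponsor's own planning value.
- Give an expected loss and raise the minimum to 40 / (1 − loss), which is 45, 50 or 58 at 10%, 20% or 30%.

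The second option costs only wording and needs no extra patients, but the stated power becomes less favourable. The first and third also need higher recruitment in any country that would otherwise stop at 40. The target of 860 leaves room for that on average, since the mean is about 72 per country.

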#### Intervention

Although C4D adapts the intervention features to country-specific guidelines, contexts and needs, there is an overall approach to achieve a robust, structured framework. The intervention consists of a T2DM self-management education and support group program [31], based on the I-Change model [26], and developed over 12 months, the program consists of two phases: an intensive phase followed by an aftercare intervention, each lasting 6 months.

The intensive phase provides participants with theoretical content and practical activities on the 4 pillars - nutrition, physical activity, sleep and relaxation - of RD2N best practice (Fig. 3). Activities and workshops related to this content include interpretation of changes in glucose levels throughout the day, biometric feedback, physical exercises, relaxation and coaching practices, and cooking classes. C4D provide people living with T2DM with skills for incorporating healthy habits into their lifestyles in an experiential dynamic way (i.e. participants must ‘live’ and practice the concepts they receive during the theoretical sessions). For pedagogic and organizational reasons people living with T2DM will be organized into groups of 20 people approximately.

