**Fig. 3 Fig3:**
[figure not shown]
Pillars of C4D intervention

The intensive phase tests two different delivery modes with identical content, one face-to-face and the other telematic, supported by a digital platform in both cases. The face-to-face modality refers to interventions consisting of about 6 on-site group training sessions over 6 months. A novel aspect of C4D is the inclusion of an overnight stay in order to: (a) promote group bonding, through joint acquisition of the knowledge received and its practice; (b) focus attention, by taking participants out of their own environment, responsibilities and situation at home; (c) aid follow-up, as the stay would allow for greater control over program follow-up (fewer triggers in the program environment, such as e.g., snacking); (d) guarantee for safety, as participants would feel physically and emotionally safe (especially participants on hypoglycaemic medication); (e) ease the burden, as the two start days are fully scheduled and intensive. Conversely, the telematic modality refers to several fully digital group sessions. The online platform will offer support throughout the duration of both intervention modalities, including coaching, close personal advice, and physician-monitoring of medication use.

The aftercare intervention over the following 6 months ensures that barriers are removed, and new habits become sustainable over time. Integrating T2DM self-care into daily life is a challenge for participants and their families. Therefore, individual participant characteristics, social determinants of health, and psychosocial factors should be part of the person-centered care, respecting, and responding to their individual preferences and barriers [1].

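### The minimum of 40 per country is sized as 40 independent participants but consists of about two training groups of 20, so the stated 80% power and 5% error rate hold only if outcomes within a group are uncorrelated

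*Protocol article*

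**What the plan says.** Under Recruitment of participants, the protocol article expects 860 participants with at least 40 per country and takes body weight as the main outcome for sizing. It states that "a sample size of 40 participants is sufficient for a paired sample t-test (power of 80%, type 1 error rate 0.05"), taking the 6-month weight results of the original programme "with standard deviation of 5.1 kg" and "assuming the true effect size (mean reduction in body weight during the first 6 months) is 2.3 kg". That section mentions no correlation between participants, design effect or other allowance for clustering.

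Under Intervention, the article says that "people living with T2DM will be organized into groups of 20 people approximately". Both delivery modes, face-to-face and telematic, use group sessions. Table 1 gives the coach or facilitator the task "Activate and monitor group dynamics". One stated purpose of the overnight stay, which belongs to the face-to-face mode only, is to "promote group bonding, through joint acquisition of the knowledge received and its practice". The Discussion adds that peer groups are expected to reinforce and support their members.

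**The concern.** A paired t-test on weight change is a one-sample t-test on the changes, and its standard error is right only if the changes are independent. Participants who share a coach, a schedule and a peer group will tend to change together, and the article presents that shared influence as part of how the programme works. If it does work that way, the variance of a country's mean change is larger than the test assumes. The rejection rate under no change then exceeds 5%, and the intervals are too narrow. At the country minimum there are only about two groups, so that country's own data say almost nothing about between-group variation. At stake is the claim that each country at the minimum has 80% power at a 5% error rate, and the width of any interval, by country or pooled, that ignores the groups.

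**Working it through.** **Inputs.** From the article: mean change 2.3 kg, SD 5.1 kg (read as the SD of the 6-month change), α = 0.05, power 80%, at least 40 per country, 860 in total, groups of about 20. Sidedness is not stated; two-sided reproduces the figure. Assumed, because the documents give none: ICC of weight change 0.01 / 0.02 / 0.05.

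**1. The plan's own figure.** Normal formula: n = (5.1 × (1.960 + 0.842) / 2.3)² = 6.213² = 38.6, so 39. The exact t calculation gives 41. At n = 40 the noncentrality is (2.3/5.1) × √40 = 2.852 on 39 df, and power is 79.4%. One-sided would need only 31 or 32. The stated 40 is therefore correct under independence, with nothing in reserve.

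**2. Design effect for groups of 20.** DE = 1 + (20 − 1) × ICC. The true standard error of the mean change at n = 40 is 5.1 × √(DE/40), against 5.1/√40 = 0.81 kg under independence.

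**3. The ordinary paired t-test with two groups of 20.** Simulated with a random group effect, total SD held at 5.1 kg, 200,000 runs per ICC. At ICC 0 it returns 5.0% type I error and 79.5% power, as it should.

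**4. A test of that country alone that respects the groups.** Two group means leave 1 df, with critical t 12.71. The noncentrality is 2.3 divided by the true standard error, for example 2.3/1.13 = 2.04 at ICC 0.05. Even at ICC 0 this test has only about 18% power.

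| Assumed ICC | 0.01 | 0.02 | 0.05 |
|---|---|---|---|
| Design effect | 1.19 | 1.38 | 1.95 |
| True SE, n = 40 (kg) | 0.88 | 0.95 | 1.13 |
| Type I error, ordinary paired t-test | 7.2% | 9.4% | 16.2% |
| Its power for 2.3 kg, at that error rate | 78% | 76% | 73% |
| Power, group-level test on 1 df | 16% | 15% | 13% |
| Groups of 20 for 80% power, group-level test | 5 | 5 | 6 |

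**5. Pooled sample.** 860/20 = 43 groups. SE = 5.1 × √(DE/860) = 0.19 / 0.20 / 0.24 kg, against 5.1/√860 = 0.17 kg under independence. At ICC 0.05, 2.3/0.243 = 9.5 standard errors, so power exceeds 99%. Adding an assumed between-country SD of 1 kg over 12 equal countries gives √(0.243² + 1/12) = 0.38 kg, and power is still above 99%. A pooled paired t-test that ignores groups has a type I error of about 2 × [1 − Φ(1.96/√DE)] = 7.2% / 9.5% / 16.0%. Its intervals are 1/√DE = 92% / 85% / 72% of the proper width.

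**The case against.** The strongest reply is that the t-test appears only in the sample-size sentence. A simple formula used for sizing does not fix the analysis, and an analysis plan that is not shown may specify a clustered model. That stands as far as the error rate goes: such a model would repair it. It would not restore the stated 80% power in a country with two groups, and that claim is in the article itself.

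Second, 40 is a floor. The average is 860/12, about 72 per country, and the figure with country minima is not shown, so how many countries sit at 40 is unknown. This also stands. The loss of power is worst at the floor and smaller above it. The inflation of the error rate does not shrink as groups are added, as the pooled case shows.

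Third, the ICC is assumed, the bonding text covers one delivery mode, the pooled result is secure, and the Discussion already concedes that an uncontrolled design limits causal claims. All of this limits the seriousness of the point without removing it.

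Two stronger readings are tempting and should not be drawn. A reader might apply the design effect to the sample size and conclude that the planned test has about 74% / 68% / 53% power. Those values (normal approximation) belong to a test in which the design effect is known. The ordinary paired t-test ignores it and has the 78% / 76% / 73% in the table. A reader might also infer, from the country minimum and from the statement that "Conclusions about acceptance and effectiveness in different contexts will allow the production of guidelines for transferability of the intervention in the EU", that 12 country p-values will be compared and that the guidelines will follow whichever reach significance. The article says neither. It bases transfer on implementation frameworks, process and qualitative data, and costs.

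**Conclusion.** The point holds for the sample-size rationale and should be fixed, though it does not threaten the main result. The stated power and error rate for 40 participants are right only at an ICC of zero, which sits badly with a programme that relies on group interaction. Over an assumed ICC of 0.01 to 0.05, the true error rate of the ordinary test at the country minimum is about 7% to 16%, and a group-respecting test of that country alone has about 16% down to 13% power. These sizes rest on groups of exactly 20, two groups per country at the floor, and the assumed ICC. The pooled sample remains more than large enough to detect 2.3 kg, provided its standard error accounts for the groups.

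**What to change.** - Record a training-group identifier for every participant. This has to be captured during data collection.
- Make the pooled 6-month weight change, with training group accounted for, the powered analysis. A mixed model with group and country effects, or cluster-robust errors with a small-sample correction, would both serve.
- Restate power for that analysis over a declared ICC range, for example an SE of about 0.24 kg at ICC 0.05.
- Describe 40 per country as a precision floor. Report country results as estimates with intervals and withdraw the 80% power claim at that level.

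The cost is wording, analysis code and one data field, with no added participants. The downside is that the country-level claim becomes less favourable than the one now printed.
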